### Description of rapid tests to be used

Malaria rapid tests are already available at all PHCs as part of standard care. In addition, semiquantitative lateral flow CRP tests will be available for healthcare workers to use on eligible patients at intervention arm PHCs when prompted by EDAM. If a patient agrees to these tests, a finger-prick blood sample will be taken by the healthcare worker and placed onto the test kit in accordance with manufacturer instructions. Refusals will be recorded in the EDAM app. Other than these finger prick samples as part of the clinical management algorithm, no other samples will be taken. CRP test kits and associated consumables will be restocked on a monthly basis and checked to confirm they are properly used for study purposes only. The training for healthcare workers will emphasise respect for patient autonomy and that refusal on their part to be tested should be accepted without reservation. Reasons for patient refusal to be tested will be noted in the app to inform future algorithm development and community engagement activities.

The CRP rapid test which will be used is the Actim CRP test from Medix Biochemica (Finland; ISO certification ISO13485:2016).^28^ Much like a malaria rapid test, it is a simple lateral flow device that uses capillary blood, obtained through a finger-prick or heel-prick and provides a semiquantitative indication of whether CRP concentrations are <10 mg/L, between 10 and 40 mg/L, between 40 and 80 mg/L or >80 mg/L, in under 5 min with minimal training requirements. It meets European Union standards (CE-marking) as well as the regulatory requirements of 13 other countries and has been validated for accuracy in previous studies.^26 29^ The pulse oximeter which will be used is a Lifebox-Smile Train hand-held device, which is specifically manufactured to be durable for use in resource-limited settings,^30^ and which has been successfully used in SEACTN. Lifebox is a non-governmental organisation whose goal is to improve anaesthesia safety through the distribution of pulse oximeters developed for use in low-resource settings. Medix Biochemica and Lifebox played no role in the design of this study, and the investigators declare no conflicts of interest with respect to the choice of these point-of-care aids.

### Outcome measures

The primary outcome measure is the proportion of patients with AFI who are prescribed antibiotics in routine primary healthcare at initial presentation in the intervention and control arms.

Several secondary outcome measures will also be assessed:

The proportion of patients with full recovery at 7 and 14 days in intervention and control PHCs.The proportion of patients referred to hospital at presentation in intervention and control PHCs.The proportion of patients in intervention PHCs whose management followed the EDAM recommendations.The proportion of patients with unplanned re-presentations to any healthcare facility at 7 and 14 days (if not fully recovered by 7 days) in intervention and control PHCs.The proportion of patients prescribed antibiotics by a healthcare provider or who independently purchased antibiotics during the follow-up period, as determined by self-report, in intervention and control PHCs.The proportion of patients with severe clinical outcomes (death or hospitalisation) at 7 and 14 days (if not fully recovered by 7 days) in intervention and control PHCs, not including those referred to hospital at presentation.The proportion of patients prescribed an antibiotic in intervention PHCs by CRP level (<10 mg/L, between 10 and 80 mg/L, >80 mg/L).The usability and acceptability of EDAM for healthcare workers (a separate ethical approval application will be made for this work).The cost-effectiveness of EDAM compared with routine care.

Interpretation of the outcomes will consider the contextual factors inherent to the Cambodian primary care landscape, as described by Chew *et al*.^31^ In addition, the usability and acceptability of EDAM will be measured using structured interviews conducted with the healthcare workers in the intervention arm; this study does not form part of this protocol and will have its own ethical approval, as mentioned previously.

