The proposed study and intervention meet all of these criteria. The infeasibility of obtaining extensive informed consent from each potential participant by research staff has already been explained. In support of this argument, Sim and Dawson, and Dal-Ré and colleagues, state that waiving informed consent is justifiable when the methodological integrity of the study is brought into question.^22 23^ In order for healthcare systems to be responsive and improve patient care implementation, studies are required to generate evidence for policy change and to ensure that the benefits seen in research settings are translated into routine care. There is precedent for this waiver, as illustrated by a similar cluster-randomised trial performed recently in Vietnam.^4^ Thus, instead of obtaining written informed consent, which would also disrupt patient care, verbal assent will be obtained prior to the performance of rapid malaria diagnostic and CRP tests, as is usual in clinical practice, and to allow follow-up by research staff. The drawing of fingerprick blood for malaria and CRP rapid tests is also of minimal risk and the blood taken is only being used for direct patient care. Similar to other tests that may be indicated, patients or their legal guardians will be able to refuse these tests, without any other impact on their care.

The research question is of high clinical importance and social value, helping to guide more appropriate antibiotic prescribing by both reducing unnecessary antibiotic prescribing in the community, a key driver of AMR,^24 25^ and identifying patients who need referral to hospital and/or antibiotics but may be missed by routine clinical assessment. The EDAM app offers these potential improvements with a low-risk intervention, that could be rapidly scaled up. Indeed, the components of EDAM (which are described fully below and include pulse oximetry, malaria and CRP rapid tests combined with clinical symptom-based guidelines) have each individually been determined to be of minimal risk and are already widely used for these purposes in other settings. Furthermore, large clinical trials of similar, but not identical, eCDSAs with extensive patient follow-up have been shown to be effective in primary care settings elsewhere.^8 26^

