The patient meets eligibility criteria and has no danger signs, either measured by the health worker or observed by any of the health worker, patient or caregiver (table 1). In this case, the patient will be enrolled and EDAM will guide the healthcare worker through the in-built algorithm leading to a suggested initial management plan, which will include a malaria rapid test as per local policy. The selection of relevant observed danger signs (e.g., convulsions) was based on established national and international clinical guidelines and ratified by a panel of local expert clinicians. All management plans were also devised by local expert clinicians with regard to local guidelines and approved by the relevant health authority.The patient meets eligibility criteria and has one or more measured or observed danger signs. In this case, EDAM will recommend a malaria rapid test and empirical antibiotic prescription (the choice of which will depend on local guidelines) and immediate referral to hospital. The patient will be enrolled and the algorithm will end here.The patient does not meet eligibility criteria. In this case, EDAM will inform the healthcare worker that it is not appropriate to be used for this patient and that they should revert to their usual practice in dealing with non-acutely febrile patients. The patient will not be enrolled and the algorithm will end here.

**Table 1 T1:** Measured and observed danger signs by age group for patients enrolled into the study

Age group	Measured danger signs	Observed danger signs
Children aged ≥1 to <5 years	Voice/pain/unresponsive on Alert, Verbal, Pain, Unresponsive (AVPU) scale SpO_2_<90% Severely abnormal heart rate (pulse of <80 or >160 beats per minute)	Unable to drink anything or breastfeed Vomiting everything Generalised convulsions Unable to sit upright/stand/walk (when previously able)
Children aged 5 to <15 years	Voice/pain/unresponsive on AVPU scale Severely abnormal heart rate (pulse of <70 or >150 beats per minute (5 to <12 years) or <50 or >130 beats per minute (12 to <15 years)) Fast breathing (respiratory rate of ≥40 breaths per minute (5 to <12 years) or ≥30 breaths per minute (12 to <15 years)) SpO_2_<90%	Unable to drink anything Vomiting everything Generalised convulsions Unable to sit upright/stand/walk independently New-onset confusion

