Healthcare workers in intervention arm PHCs will be provided with face-to-face training on the use of EDAM. They will also be taught how to use pulse oximeters and CRP rapid tests, which are not available in control arm PHCs, as well as trained on measuring blood pressure, respiratory rate and pulse rate, and assessing level of consciousness. Training will be conducted by the study team in the relevant local language prior to patient recruitment, with refresher training conducted on the advice of site coordinators or study monitors. Contact details of the study coordinator and/or field supervisor will be provided to PHCs; these personnel will be available for advice should any queries regarding the study arise.

To maintain clinical practice and workflows at control arm PHCs as close to the current standard of care as possible, the only extra activity for the trial required of healthcare workers in the control arm is screening and data collection. They will receive a simplified version of the EDAM app which will allow them to log patient demographic details as well as conduct patient screening and enrolment, but does not contain the clinical decision support algorithms present in the version used in the intervention arm. Control arm healthcare workers will receive training in the use of the simplified EDAM app, but not in the clinical procedures and use of point-of-care aids that healthcare workers in the intervention arm are taught.

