One important caveat is that patients who re-present during the follow-up period will be considered as unscheduled attendances secondary to the initial diagnosis, given that unscheduled attendance is a secondary outcome measure. This will also allow determination of whether antibiotics are initially withheld and then given at a subsequent visit. The major limitation of this approach, however, is that some patients may be categorised as unscheduled presentations when their subsequent visit is actually for a new problem or illness.

The trial schedule of enrolment, interventions and assessments, completed using the Standard Protocol Items: Recommendations for Interventional Trials (SPIRIT) guideline template,^27^ is shown in table 2. The completed SPIRIT checklist can be found in online supplemental information S2.

**Table 2 T2:** Schedule of enrolment, interventions and assessments

Timepoint (DAY)	Study period			
	Enrolment	Clinical encounter	Follow-up	
	0	0	7	14
Enrolment:				
Eligibility screen	X			
Interventions:				
EDAM app		X		
Standard of care		X		
Assessments:				
Antibiotic prescription		X		
Hospital referral		X		
Recovery by day 7			X	
Recovery by day 14 (if not recovered by day 7)				X
Death or hospitalisation* by day 7			X	
Death or hospitalisation* by day 14 (if not recovered by day 7)				X
Re-presentation by day 7			X	
Re-presentation by day 14 (if not recovered by day 7)				X
Antibiotic consumption† by day 7			X	
Antibiotic consumption† by day 14 (if not recovered by day 7)				X

* If not referred to hospital at the time of clinical encounter.

† If not prescribed antibiotic at the time of clinical encounter.

EDAM, Electronic clinical Decision support for Acute fever Management

The trial commenced in May 2024. The end date is dependent on the rate of patient enrolment but will be no later than May 2025.

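### The severe-outcome endpoint leaves out patients referred at presentation, a step after randomisation that EDAM is meant to change, so its comparison of arms is not randomised and can be biased in either direction

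*Protocol article*

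**What the plan says.** Under Outcome measures, the article lists as a secondary outcome the proportion of patients with "severe clinical outcomes (death or hospitalisation) at 7 and 14 days (if not fully recovered by 7 days"), taken "in intervention and control PHCs, not including those referred to hospital at presentation". In Table 2 (Description of other study procedures and follow-up), the rows for death or hospitalisation carry the footnote "If not referred to hospital at the time of clinical encounter".

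The same list of outcomes contains "The proportion of patients referred to hospital at presentation in intervention and control PHCs". Under Description of intervention, the relevant branch begins: "The patient meets eligibility criteria and has one or more measured or observed danger signs". For these patients EDAM recommends a malaria test, an empirical antibiotic and, in the article's words on the last two, a choice that will "depend on local guidelines) and immediate referral to hospital". They are enrolled. The same section says that intervention staff are taught to use "pulse oximeters and CRP rapid tests, which are not available in control arm PHCs", and are trained in measuring blood pressure, respiratory rate and pulse and in assessing consciousness. Control staff do not receive that training. The Design section gives as one aim of the research "identifying patients who need referral to hospital and/or antibiotics but may be missed by routine clinical assessment".

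The Abstract says that the day-7 follow-up is there to establish EDAM's safety profile. Under Description of statistical analyses, secondary endpoints are to be handled much as the primary one: logistic regression with treatment as a fixed effect and health centre as a random effect.

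**The concern.** Randomisation makes the arms comparable in all enrolled patients. It does not make them comparable in a subset defined by something that happens later and that the intervention influences. Non-referral at presentation defines such a subset. If EDAM changes who is referred, as the Design section expects, the patients left in the endpoint differ between arms in how ill they were at the start. A random effect for health centre does not correct this.

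The wording also removes referred patients altogether, so their deaths go with their admissions. A patient who is referred, never reaches hospital and dies would not count. This is the only severe-outcome comparison listed, for a tool intended to reduce antibiotic prescribing, and it is the result that readers will use to judge safety. The definition stands in the article itself, so this is not a detail left to the analysis plan.

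**Working it through.** **Inputs from the article.** 15 centres per arm and 152 patients per centre give 15 × 152 = 2,280 per arm. That target reproduces: 25% against 17.5%, two-sided 0.05 and 80% power need 466 per arm without clustering. With an intraclass correlation of 0.025, m = 466 × 0.975 / (15 − 466 × 0.025) = 135.6, rounded up to 136; 136 / 0.9 = 151.1, rounded up to 152; 152 × 30 = 4,560. No sample size or power is given for the severe outcome. The only risk quoted is about 1.5% (Sample size calculations). It belongs to a different composite, which includes hospitalisation for longer than 3 days and symptoms persisting at 28 days, so it serves here only as an order of magnitude.

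**Inputs that are assumed.** The article does not say what share of eventual severe cases is referred at presentation in either arm (s), or what share of other patients is referred (f). I vary s from 20% to 60% and set f = 2% in both arms. The true risk r is held at 1.5% in both arms, so the true risk ratio (RR) is 1.0.

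**Formula.** Risk among the non-referred = r(1 − s) / [r(1 − s) + (1 − r)(1 − f)].

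Control, s = 20%: 0.015 × 0.8 / (0.015 × 0.8 + 0.985 × 0.98) = 0.0120 / 0.9773 = 1.23%.
EDAM, s = 50%: 0.0075 / (0.0075 + 0.9653) = 0.77%. The ratio is 0.63.

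Events counted per arm = 2,280 × 0.015 × (1 − s) = 34.2 × (1 − s).

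| s control | s EDAM | Events counted, control v EDAM | Risk, control v EDAM | RR shown (truth 1.0) |
|---|---|---|---|---|
| 20% | 20% | 27.4 v 27.4 | 1.23% v 1.23% | 1.00 |
| 20% | 40% | 27.4 v 20.5 | 1.23% v 0.92% | 0.75 |
| 20% | 50% | 27.4 v 17.1 | 1.23% v 0.77% | 0.63 |
| 20% | 60% | 27.4 v 13.7 | 1.23% v 0.62% | 0.50 |
| 40% | 20% | 20.5 v 27.4 | 0.92% v 1.23% | 1.33 |
| 50% | 20% | 17.1 v 27.4 | 0.77% v 1.23% | 1.59 |

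The result depends little on f: with f = 2% in control and 5% with EDAM, the third row gives 0.65.

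**With a true effect.** To a close approximation, RR shown = true RR × (1 − s EDAM) / (1 − s control). At 20% v 50% the multiplier is 0.5 / 0.8 = 0.625. A true RR of 1.3 shows as 0.81, and a true RR of 2.0 as 1.25. The true RR that would show as 1.0 is 0.8/0.6 = 1.33, 0.8/0.5 = 1.6 or 0.8/0.4 = 2.0 for EDAM shares of 40%, 50% or 60%. These correspond to about 11, 21 or 34 extra severe outcomes in the EDAM arm.

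**All enrolled patients counted.** At 1.5% in both arms, 34.2 v 34.2 events and RR 1.00, whatever the referral shares.

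**The case against.** The restriction has a rationale. EDAM recommends both an antibiotic and referral when a danger sign is present, and CRP-guided withholding applies only to patients without danger signs. Harm from withholding should therefore arise mainly among patients sent home, and an admission that follows a day-0 referral is intended management. This stands as a reason to show those admissions apart. It does not explain dropping deaths, and it does not make the non-referred groups comparable.

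Counting admissions by every route has its own distortion. Suppose (assumed) that EDAM leads to 2% more patients being referred and admitted. That adds 0.02 × 2,280 = 45.6 events to about 34.2, and the ratio becomes 79.8 / 34.2 = 2.3 with no harm done. This stands, and it limits the fix: the all-route composite should not be the headline.

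Other outcomes help in part. Referral and full recovery are compared without this exclusion, and the monitoring board sees summary data in real time. None of these is an all-patient comparison of death.

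A reader might go further than the article supports in four ways:

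- **That the bias always favours EDAM, whatever the true effect.** The last two rows of the table run the other way, and at 20% v 50% a true RR of 2.0 still shows as 1.25.
- **That referred patients are not followed up.** The follow-up text exempts nobody on grounds of referral and provides for deaths to be documented. In Table 2 the asterisk sits on hospitalisation and can be read as qualifying that component only. The outcome definition is what excludes these patients from both components.
- **That patients recovered at day 7 leave the day-14 denominator.** The wording describes who is contacted again, not who is analysed.
- **That the 0.63 is an estimate.** It rests on assumed shares.

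**Conclusion.** The point holds as a defect in the definition of the safety endpoint. As written, the only severe-outcome comparison conditions on a post-randomisation step that EDAM is designed to change, and it leaves deaths among referred, enrolled patients uncompared. Neither the direction nor the size of the bias can be determined from the article. Under the assumed shares, the exclusion alone moves a true RR of 1.0 to 0.50–0.75 if EDAM refers more of the eventual severe cases, and to 1.33–1.59 if it refers fewer. If the two arms referred equal shares, both of severe cases and of other patients, there would be no bias of this kind. The primary outcome and its sample size are unaffected.

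**What to change.** - Make all enrolled presentations the main safety population, with death by day 7 as the key comparison. Deaths are only part of a severe outcome that is itself rare, so report the estimate with its confidence interval and do not take a non-significant result as evidence of safety.
- Also report death or hospitalisation in all enrolled patients, with admissions that follow a day-0 referral as a separate component, stated in advance not to count as harm on their own.
- Keep the non-referred analysis as supportive, printed beside the proportion referred in each arm.
- Align the Table 2 footnote so that outcomes of referred patients are recorded at the existing day-7 follow-up. The listed hospitalisation question is tied to re-presentation, so check that it also captures admission after a day-0 referral.

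**Cost.** No extra visits or contacts. The outcome wording and the footnote change, and the amendment needs approval from both ethics committees. The trial has been recruiting since May 2024, so it should be made promptly, and the completeness of outcomes for referred patients already followed up should be reported. The analysis plan is due before recruitment ends and can carry the definitions. The main downside is that the composite will contain intended admissions, so it cannot be interpreted without its components.

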### Pre-trial and post-trial engagement

To gauge early policy-maker views on the potential usability and acceptability of the intervention, engagement meetings were held with key stakeholders in the Ministry of Health responsible for medical services, primary care, public health, and digital health and health informatics. Similar meetings were held with medical specialists in the field of adult internal medicine/infectious diseases, paediatrics and primary care to develop consensus clinical management plans tailored to local conditions as part of the algorithms. These management plans, as well as the overall design of the study, were further reviewed and endorsed by senior medical staff of the Battambang Provincial Health Department, and support for the trial was also obtained from the provincial government.

Taking into consideration evidence from similar eCDSAs used in other LMIC settings, such as ePOCT and inSCALE in sub-Saharan Africa,^8 32^ both groups were also asked for their views on the interface to inform the development of the EDAM app, which was then further refined by asking a small number of PHC healthcare workers to test the app and offer their opinions on its usability. These stakeholder consultations have informed the version of the EDAM app used in this study. A second round of such meetings will be conducted towards the end of the study to assess stakeholder experiences.

Before randomisation of participating PHCs, an overview of the study will be presented to all PHC healthcare workers. Education will also be provided about the role of antibiotics, AMR and good clinical practice (GCP) for research. Training specific to the study intervention has been described previously. Day-to-day field activities and monitoring will be undertaken by staff of MORU, AHEAD and the Provincial Health Department.

### Patient and public involvement

Information on EDAM for patients will be displayed in all study PHCs in the form of posters; however, patients were not involved in the design, conduct, reporting or dissemination plans of the study. Nonetheless, local engagement was undertaken to the extent possible via the activities described above.

### Sample size calculations

There is scant reliable routinely collected data on antibiotic prescription in the study PHCs. The baseline rate of antibiotic prescription was based on the findings from SEACTN, which includes PHCs where the proposed trial will be run,^12^ where data on patients prescribed antibiotics for AFI have been systematically collected since 2021. In the PHCs participating in this planned interventional study, the mean proportion of acutely febrile patients prescribed antibiotics was approximately 25%. The ICAT cluster-randomised trial, in which the proportion of patient recruited by age group was broadly similar to that seen in SEACTN, showed that the use of CRP rapid tests reduced the antibiotic prescription rate by 36%.^4^ Therefore, it is estimated that EDAM will result in a reduction of antibiotic prescription from 25% to 17.5%.

PHCs participating in SEACTN will also participate in this study if they meet criteria for inclusion. Other PHCs will be selected for inclusion in this study, if required, to make up a total of 15 PHCs in each of the control and intervention arms per country, on the assumption that their antibiotic prescription rates are also broadly similar. The PHCs will be drawn from across three Operational Districts as defined by the Battambang Provincial Health Department, with 10 selected from each operational district. As mentioned previously, each PHC will be treated as a cluster. Given the above, the sample size calculations are based on probabilities of 0.05 and 0.2 for type I and type II errors, respectively, and an intraclass correlation coefficient of 0.025, as is common for cluster randomised trials of this nature.^6 33^ Based on the parameters mentioned previously, with 15 clusters per arm the target number of patients to be recruited per cluster is 152 while assuming a drop-out rate of 10%. In total, therefore, the target number of patients to be recruited is 4560. Sample size calculations were performed in Stata V.18.

Stratified cluster randomisation of PHCs by operational district was performed; as mentioned previously, 10 clusters were included per district. A pseudorandomisation list of allocations to one of two possible arms (‘A’ or ‘B’) was generated using the *ralloc* package in Stata V.18.0 (StataCorp). This list was merged 1:1 with a list of PHCs. Assignment of arms ‘A’ and ‘B’ as either intervention or control was performed using the flip of a coin, with arm ‘A’ designated as the intervention arm if the coin flip came up heads and vice versa.

The study is not powered to detect differences within each age group, but subgroup analyses will be conducted among patients aged ≥1 to <5 years (younger children), 5 to <15 years (older children) and ≥15 years (adults). While inclusion of safety endpoints as coprimary objectives was also considered, based on SEACTN data the absolute risk of a severe outcome, defined as death or hospitalisation for longer than 3 days or persistent symptoms at 28 days post presentation, is minimal (approximately 1.5%).

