### Description of statistical analyses

The primary endpoint is the proportion of patient consultations for AFI which result in antibiotic prescription. The primary comparison between the treatment arms will be a logistic regression with the treatment assignment as a fixed effect, and the PHC as a random effect. P values (two-sided) below 0.05 are considered significant. A two-sided 95% CI for the OR of being prescribed antibiotics will be calculated.

The primary endpoint (proportion of patients given an antibiotic prescription) will also be investigated by subgroup to assess whether any change in antibiotic prescribing is homogeneous across subgroups. Specifically, intervention effects and appropriate tests for heterogeneity will be calculated in the following predefined subgroups:

Age: younger children aged ≥1 to <5 years, older children aged 5 to <15 years and adults aged ≥15 years.Sex at birth: male or female.Patients with a documented fever or hypothermia at presentation versus patients without.

The secondary endpoints will be analysed in a similar manner to the primary endpoint. A detailed Statistical Analysis Plan will be developed prior to the completion of recruitment for the study.

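### The stated primary model leaves out the randomisation stratum and the PHCs' known past prescribing, the two covariates that could reduce the between-PHC variance limiting this trial's power

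*Protocol article*

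**What the plan says.** Sample size calculations names SEACTN as the source of the baseline rate. It describes SEACTN as a study that includes PHCs of this trial and "where data on patients prescribed antibiotics for AFI have been systematically collected since 2021". What it takes from that source is one mean: "In the PHCs participating in this planned interventional study, the mean proportion of acutely febrile patients prescribed antibiotics was approximately 25" per cent. PHCs outside SEACTN may be added if needed. Their number is not given, and their rates are assumed to be broadly similar.

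The ICC comes from elsewhere: "an intraclass correlation coefficient of 0.025, as is common for cluster randomised trials of this nature", with two citations. The same section says that randomisation was stratified by operational district, with ten PHCs in each of three districts.

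Description of statistical analyses gives the primary comparison as a "logistic regression with the treatment assignment as a fixed effect, and the PHC as a random effect". No other term is named. A detailed statistical analysis plan is to be written before recruitment ends.

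**The concern.** With 30 clusters, precision depends mainly on how much PHCs differ from one another, and much less on how many patients each one enrols. A PHC's own past prescribing is the natural predictor of its prescribing during the trial, and records exist for at least some of these PHCs. The model as written does not use them, and it also omits the factor that the randomisation was stratified by.

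Two things are at stake. The first is power, particularly if the true ICC exceeds 0.025. The second is chance imbalance. Under the plan's inputs, the control-arm SD of PHC rates is √(0.025 × 0.25 × 0.75) = 6.8 percentage points. The difference in mean underlying rate between two arms of 15 PHCs then has an SD of 6.8 × √(2/15) = 2.5 points, one third of the 7.5-point target effect. District stratification removes only the part of this that lies between districts.

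**Working it through.** **Inputs from the article.** "probabilities of 0.05 and 0.2 for type I and type II errors, respectively"; "P values (two-sided) below 0.05 are considered significant"; "reduction of antibiotic prescription from 25% to 17.5" per cent; ICC 0.025; "with 15 clusters per arm the target number of patients to be recruited per cluster is 152 while assuming a drop-out rate of 10" per cent. The baseline-to-trial correlation r is not in the article. It is an assumption, shown over a range.

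**1. Reproduce the plan's figure.**
- Two proportions, 0.25 v 0.175, two-sided 5%, 80% power, no continuity correction: n = 465.8, so 466 per arm under individual randomisation.
- Patients per PHC: m = n(1 − ICC)/(15 − n × ICC) = 465.8 × 0.975/(15 − 11.65) = 135.4, so 136.
- Drop-out: 136/0.9 = 151.1, so 152. Total: 30 × 152 = 4560.

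This matches exactly. Power by z is 80.1% with 137 analysed per PHC (152 × 0.9) and 81.0% with all 152. By t with 28 df and 152 per PHC it is 78.4%. The z and t figures differ because of the reference distribution; the plan's calculation contains no mistake.

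**2. The ceiling.** As m grows, the effective size per arm tends to 15/ICC = 15/0.025 = 600. Noncentrality = 0.075 × √(600/0.331875) = 3.19, where 0.331875 = 0.25 × 0.75 + 0.175 × 0.825. Power is 86.8% by t (28 df) and 88.9% by z. Doubling to 274 analysed per PHC gives 84.5% by z. At ICC 0.05 the ceiling is 58.6% by t and 61.3% by z.

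**3. Adjust for the baseline rate.** If the baseline rate explains a share r² of the between-PHC variance, the effective size per arm is

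n_eff = 15m / [(1 − ICC) + m × ICC × (1 − r²)].

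With m = 152, t with 27 df and a baseline rate for every PHC:

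| r | n_eff, ICC 0.025 | Power | n_eff, ICC 0.05 | Power |
|---|---|---|---|---|
| 0 (unadjusted) | 477 | 78% | 267 | 54% |
| 0.2 | 493 | 80% | – | – |
| 0.3 | 514 | 81% | – | – |
| 0.4 | 547 | 84% | – | – |
| 0.5 | 596 | 86–87% | 343 | 64% |
| 0.7 | 783 | 94% | 472 | 78% |

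ICC 0.05 is a what-if value; nothing in the article points to it.

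**4. When does adjustment beat any number of patients?** Setting n_eff above 15/ICC gives r² > (1 − ICC)/(m × ICC). At ICC 0.025 and 137 analysed this is 0.975/3.425 = 0.285, so r above about 0.53. With all 152 it is 0.257, so r above about 0.51. The table agrees: at r = 0.5 power is 86.5%, just under the 86.8% ceiling by t.

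**5. What reduces the gain.**
- *Coverage.* Scaling r² roughly by the share of PHCs with past data, r² = 0.50 gives 94.9% with full coverage and 87.8% if half lack data (z, 137 analysed).
- *No persistence.* A simulation of PHC-level logits (4000 runs, 137 analysed and an assumed 300 baseline patients per PHC, t reference) gave 81% unadjusted and 79% adjusted at r = 0. In the same simulation adjusted power was 85% at r = 0.5 and 92% at r = 0.7.

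No figure is given for district, because the article reports no district-level rates.

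**The case against.** The strongest reply is that a random-PHC logistic model without covariates is valid, that covariates are commonly settled in the analysis plan, and that the plan is still to come. This stands in part. The omission is a lost efficiency, and the later plan may cure it. But the article does more than stay silent: it writes out the primary comparison, and that model leaves out the stratification factor.

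The second reply is that the benefit is unproven, which is right. No correlation is reported. SEACTN recruited all ages and also used village health workers, whereas the trial takes patients aged one year or more at PHCs. Staff at all PHCs are taught about antibiotics and resistance before randomisation. Each of these could weaken the link between past and trial-period rates.

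A reader might infer more than the article supports in three ways:
- *That the trial is undersized.* It is not, on its own inputs.
- *That the ICC is wrong.* It rests on two cited sources that are not at hand, and nothing in the article shows another value.
- *That adjustment is sure to deliver power that more patients could not.* This holds only above a correlation of about 0.53; below it, more patients per PHC could match the gain.

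Nor does the article say that a usable past rate exists for all 30 PHCs.

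**Conclusion.** The point stands as a conditional gain in efficiency, with no error in the sample size. At ICC 0.025 the design is close to what 15 PHCs per arm can deliver: about 78% by t at 152 per PHC, against a limit of about 87% (89% by z). Adjusting for past prescribing acts on the variance that sets this limit. It would be worth about 1 to 5 percentage points at correlations of 0.2–0.4, about 8 at 0.5 and about 16 at 0.7. These figures assume a rate for every PHC and are smaller otherwise. If past prescribing does not predict trial-period prescribing, the gain is nil or a loss of one or two points. Including district needs no such assumption to justify it, since the randomisation was stratified by it.

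**What to change.** Before unblinding, prespecify the primary model with two fixed covariates besides arm, keeping PHC as a random effect:
- operational district;
- the PHC's pre-trial SEACTN prescribing proportion on the logit scale, with a stated rule for PHCs without data, such as the district mean plus a missing-data indicator.

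Also estimate the ICC from the SEACTN PHC-level data, report it with its uncertainty, and restate power over that range. The same data can indicate how stable PHC rates are over time, and so whether the covariate is worth including.

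The cost is analysis wording and the use of data already collected. Three districts take two degrees of freedom, and the baseline rate takes one or two. There is a small loss of power if the baseline rate is not prognostic. Randomisation is complete and recruitment began in May 2024, so the number of PHCs would not change.
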